## Abstract

**Background:**

Reducing neonatal-related deaths is one of the major bottlenecks to achieving Millennium Development Goal 4. Studies in Asia and South America have shown that neonatal mortality can be reduced through community-based interventions, but these have not been adapted to scalable intervention packages for sub-Saharan Africa where the culture, health system and policy environment is different. In Uganda, health outcomes are poor for both mothers and newborn babies. Policy opportunities for neonatal health include the new national Health Sector Strategic Plan, which now prioritizes newborn health including use of a community model through Village Health Teams (VHT). The aim of the present study is to adapt, develop and cost an integrated maternal-newborn care package that links community and facility care, and to evaluate its effect on maternal and neonatal practices in order to inform policy and scale-up in Uganda.

**Methods/Design:**

Through formative research around evidence-based practices, and dialogue with policy and technical advisers, we constructed a home-based neonatal care package implemented by the responsible VHT member, effectively a Community Health Worker (CHW). This CHW was trained to identify pregnant women and make five home visits - two before and three just after birth - so that linkages will be made to facility care and targeted messages for home-care and care-seeking delivered. The project is improving care in health units to provide standardized care for the mother and the newborn in both intervention and comparison areas.

The study is taking place in a new Demographic Surveillance Site in two rural districts, Iganga and Mayuge, in Uganda. It is a two-arm cluster randomized controlled design with 31 intervention and 32 control areas (villages). The comparison parishes receive the standard care already being provided by the district, but to the intervention villages are added a system for CHWs to visit the mother five times in her home during pregnancy and the neonatal period. Both areas benefit from a standardized strengthening of facility care for mothers and neonates.

**Discussion:**

UNEST is designed to directly feed into the operationalization of maternal and newborn care in the national VHT strategy, thereby helping to inform scale-up in rural Uganda. The study is registered as a randomized controlled trial, number ISRCTN50321130.

## Background

Maternal and neonatal illness represent some of the most important health conditions in Uganda and in sub-Saharan Africa (SSA). Globally, of the 7.6 million deaths of children under five years each year [1], 3.6 million (41%) are deaths of babies in the neonatal period, and 98% of these deaths occur in developing countries. Although recent reports show some improvements in maternal mortality globally from the current estimate of 342,900 maternal deaths worldwide in 2008, down from 526,300 in 1980 [2], there has been minimal change in sub-Saharan Africa [2].

Most neonatal deaths, or death within the first month of life, take place on the day of delivery; between 30 and 50% of newborn deaths in Africa are on the first day of life, and 75% occur in the first week alone. The same is true for maternal deaths - approximately 50% of maternal deaths take place within one day of childbirth. A number of factors contribute to this high maternal and newborn mortality including the low (37%) skilled attendance at births, poverty, HIV/AIDS, low-quality antenatal and delivery care, and the unavailability of postnatal care on the continent, as most births occur at home due to problems related to inaccessibility to care.

Despite high use of antenatal care (ANC) (94% for the first ANC visit) in Uganda [3], deliveries at health facilities have remained low (42%), and Emergency Obstetric Care (EmOC) met need is only 14%. Postnatal care (PNC) coverage is very low and maternal mortality, perinatal and neonatal mortality have remained high (maternal mortality ratio 435 per 100,000 live births, perinatal mortality 36 per 1,000 and neonatal mortality 29 per 1,000 live births) [3].

To date, most efforts to improve maternal and newborn health in Uganda have focused on influencing the supply side, usually involving training of health workers, provision of supplies, and health education. Few interventions have been directed at influencing the community or the demand side. Previous efforts in safe motherhood and child health generally neglected newborn care, with the consequence that efforts to achieve Millennium Development Goal (MDG) 4 are currently greatly constrained by a relatively high proportion of neonatal deaths. In addition, focus has been on facility-based care with limited linkages between the facilities and the community.

Based on experiences from Asia, there is now accumulating evidence of the potential for community health worker (CHW) programmes to reduce newborn deaths, even in weak health systems [4,5]. However, there is a lack of adequate successful experiences from sustained and nationwide CHW programmes, especially in SSA. Based on estimates from *The Lancet* Neonatal Survival Series, outreach and family-community care at 90% coverage could avert a substantial number of neonatal deaths [6], suggesting a potential application for programmes aimed at saving newborn lives in weak health systems such as those in sub-Saharan Africa (SSA).

In trial settings conducted mainly in Asia, neonatal mortality was reduced by an average of 30% through home visits by trained community health workers to promote preventive care and/or to provide curative newborn care [7-16]. This strategy of improving maternal/newborn care in low-income countries is also recommended in a joint WHO/UNICEF statement on home visits [16].

There are fundamental gaps in knowledge on how to most effectively implement and scale up community-based interventions linked to facility care, especially in rural poor African communities with weak formal health systems. Hence there is an urgent need to adapt and evaluate culturally and regionally appropriate packages of interventions in the African setting. Community interventions to improve home practices and generate community demand for seeking care need to be matched with an adequate supply of accessible good-quality health services for mothers as well as neonates. Mechanisms to strengthen the community-facility linkage need to be defined, and ways to practically promote care seeking in the neonatal period defined. The adapted intervention package needs to be implemented, and evaluated for effects on desired practices and cost, in order to provide policy makers with information on a scalable intervention package.

## Methods

### Study aim and objectives

To adapt, develop and cost an integrated maternal-newborn care package that links community and facility care, and to evaluate its effect on maternal and neonatal practices in order to inform policy and scale-up in Uganda.

### Specific objectives

#### Formative phase

To inform on the design of a health system-linked, community-based package for mother-newborn, with a feasible delivery mechanism for the Ugandan context.

#### Evaluation phase

To implement and evaluate a community-based maternal-newborn package linked to the health facility.

1. To assess effects related to the package of key outcomes like utilization of maternal and newborn care, key household behaviours and care seeking.

2. To cost the package implementation including cost per household visit, cost per CHW trained, and cost per year of supervision.

#### Dissemination phase

To inform on the design and scale-up of community-based mother-newborn care in Uganda.

**Hypothesis: H1:** Implementation of an integrated care package of five home visits by a CHW during pregnancy and the neonatal period to deliver one-on-one health messages and promote linkage to the health facility improves the following maternal-newborn care practices by at least 20% in two years amongst the target population in rural Uganda:

• % of pregnant women attending ANC at least four times (from 40% to 60%);

• % of pregnant women who get a skilled attendance at delivery (from 30% to 50%);

• % of mothers who put nothing on the cord (to get baseline figures during formative research);

•% of newborns who are managed in skin-to-skin contact after delivery (to get baseline figures during formative research);

• % of mothers and babies who receive postnatal care (from 12% to 50%).

### The study context

Uganda is a land-locked country located in East Africa, and lies to the north along the equator. Uganda has a projected population of 32.4 million people. Landmass is about 241,038 km^2^ in size and the country has a population density of about 137/km^2^. A total of 18% of the country is occupied by open water and swamps, and 12% by forest reserves, game parks and mountains. An estimated 86% of the population live in rural areas, and practise mainly peasant farming. The country’s estimated GDP per capita is US$ 1,300 and 35% of the population is below the poverty line (lives on less than a dollar a day). Per capita expenditure on health is only US$ 12, and more than half of this is out-of-pocket expenditure. The country has a very high birth rate of 47.8 per 1,000 population, leading to a very young and dependant population, with 50% being 14 years and below. Life expectancy is 51.6 years for men and 53.8 years for women.

Since the year 2000, the delivery of health services in Uganda has been decentralized to district level. The Ministry of Health (MoH) plays a stewardship role, providing leadership, standards, funding and policies. On the other hand, districts are responsible for implementation and service delivery. Below the district level are Health Sub-Districts (HSDs), which are administrative zones with about 10 to 20 lower level health facilities. The HSD is headquartered at a health centre level IV (HC-IV), and is structurally a mini-hospital with an obstetric theatre, wards, laboratories, one to two doctors, and several nurses and midwives. However, HC-IVs in the country are operating below standards, with most obstetric theatres being non-functional due to a lack of equipment, personnel or other inputs, or just as a result of neglect. Each HSD has three to four HCs level III (HC-III), and this is the lowest level at which laboratory services, deliveries and management of newborn babies is allowable by national policy.

HCs level II (HC-II) are more accessible to the population, but they are small, outpatient-only units that cannot admit, deliver, perform laboratory investigations, or even treat sick newborn babies. At the lowest level is HC I, which lacks any physical infrastructure. A HC I is basically a collection of community volunteers, together termed the Village Health Team (VHT). They are responsible for community mobilization and linking with the formal health facilities. However, in the majority of districts, most VHTs are not functional.

### Study site

This study will take place in the Makerere University-operated Iganga/Mayuge Demographic Surveillance Site (DSS). It is located in Iganga and Mayuge districts (Figure 1). The DSS is a full member of the International Network for continuous Demographic Evaluation of Populations and Their Health (INDEPTH) A DSS is a powerful ‘population-laboratory’ for efficacy and effectiveness trials.

**Figure 1 F1:**
[figure not shown]
Map showing the location of Iganga-Mayuge districts and the Demographic Surveillance Area, Uganda.

The Iganga-Mayuge DSS started its operations in 2004 as collaboration between Makerere University and the Karolinska Institutet, Sweden on one hand, and the two host districts on the other, with seed funding from Sida/SAREC. The Demographic Surveillance Area (DSA) has a population of about 67,200 people in 63 villages, 18 parishes and 12,000 households.

Through household visits, field assistants record pregnancies, pregnancy outcomes, deaths and migrations. Since November 2005, village-based demographic scouts notify DSS verbal autopsy interviewers (VAI) of all deaths in the area as they occur on a continuous basis. The VAI visit the bereaved family a month after the event and interview a relative of the deceased who was present at the time of the illness/event and death on verbal and social autopsies (VASA). Three experienced practising doctors independently review the data and assign differential diagnoses on the cause of death according to standard criteria. If there is agreement between at least two of them, the diagnosis is accepted as the definitive cause of death. However, if they do not agree, the three doctors meet to discuss the case and attempt to reach agreement. If this is not possible the cause is coded as undetermined. Besides determination of the most prevalent causes and circumstances of death, we also use the data to profile the burden of different disease, including neonatal conditions. This data from the VASA for maternal and newborn deaths will be analysed as part of the formative research. Results will be used to identify areas in the social processes leading up to death and hence identify modifiable factors in the home or health system on which interventions can be designed.

Iganga Hospital and 13 small health units of which 2 conduct deliveries are located in the DSA. Preliminary findings from the DSA show the following: that 60% of all deaths occur outside a health facility setting; almost all (90%) deaths are due to illnesses as opposed to other causes like injuries and suicide; and the stillbirth rate is about 10/1,000 births, thus indicating under-detection of negative birth outcomes. As it is for most DSS, the first analysis has been a learning experience on the quality of the data, particularly on the reporting of pregnancies, births and newborn deaths.

### Sample and sample size

To evaluate the effect of the intervention, practice differences and changes will be determined as differences in proportions between intervention and control areas. With 80% power and 95% significance level to detect, for example, an increase in attendance four times at ANC from 40% to 60% assuming a coefficient of variation (k) of 0.25 between clusters (parishes), this will require some 60 interviews per cluster in each intervention arm for each practice survey. Similarly, to detect an increase in skilled attendance at birth from 30% to 50%, again with a k of 0.25, some 25 interviews have to be performed. To detect in increase in postnatal care from 12% to 24%, with a k of 0.25, some 30 mothers have to be interviewed. Note that the study is not powered for mortality evaluation. The number of clusters was fixed *a priori* because those were the available ones, and the sample size estimations mainly focused on the cluster size for each outcome for an 80% power.

### Overview of the trial design

#### Randomization

The unit of intervention and randomization was the village. The study area has 63 villages. All the 63 villages were eligible for randomization. Given the relatively large number of study units (63), we proposed not to stratify or match. Allocating 31 villages to intervention and 32 to comparison we thus have 31 units of intervention, each with 1 to 3 CHWs depending on the number of households therein (Figure 2). Given that the intervention is primarily through home visits by the CHW, we never anticipated contamination to be a big problem, since that would imply making extra home visits. This, however, would be monitored in the annual coverage surveys proposed. Spillover by word of mouth woman-to-woman or other would be captured as a secular trend in the comparison villages. Statistically, we believe it is advantageous to keep the unit of intervention and randomization the same. We also avoid the complexities of which outcome measure to match/stratify on.

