### Supervision of community health workers

The overall supervision is conducted by the district health teams (DHTs) of Iganga and Mayuge Districts led by the district health visitors (DHVs) in accordance with the existing district health service structure with support from the Uganda Newborn Survival Study (UNEST). Each CHW is assigned to a nearby health unit as the primary unit of referral but also the unit that will supervise her monthly.

The district supervisors, with support from UNEST, supervise the health centers/health workers using a checklist that has been developed in accordance to the national newborn standards of care

The DHVs facilitate CHWs’ group meetings with the aim of encouraging CHWs to discuss common problems and successes so that they can learn from and support each other (peer-to-peer learning). The group supervisions are held at the training sites close to the community, and involve the study team members and the CHWs’ supervisors. These meetings initially have been on a monthly basis to help the CHWs become confident and more knowledgeable.

Health workers hold individual discussion sessions with CHWs on a monthly basis at the health facility to provide support, motivation and to solve problems. Once a month, the supervisors accompany CHWs on their visits to observe how they are doing (directly observed supervision (DOS)) and provide feedback, which helps solve any problems and provides support and motivation. The health worker liaises with community leaders to solicit their opinions about and support for the work of the CHWs. This helps ensure the CHWs feel accountable to the community and that the community knows the CHW is working for them.

‘Super’ CHWs (leaders of CHWs per parish/given number of CHWs) coordinate the work of fellow CHWs in their respective parishes and communicate to the health workers any developments in the community as well as giving feedback to the CHWs.

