### Additional analyses

GIS and socio-economic data are already being collected in the DSS and thus provide a good opportunity to undertake these analyses. In the control area, data analysis will also be done by doing a before-and-after comparison to estimate the effect of only health facility improvement on maternal and neonatal care facilities. Subgroup analyses estimating separate intervention effects for facility- and home-based deliveries.

Analysis will also be done taking account of the quality of the intervention received, as assessed by the process indicators and number of visits received. Because some study participants are highly mobile and some women will move from their place of residence to their parents’ or in-laws’ houses for delivery of the baby, it is envisaged that there may be significant movements across the arms of the trial (that is, some women will move from intervention to control areas and vice versa) during the intervention period. This movement can be tracked using our surveillance system. Thus we will also compare outcomes subdividing women and newborns into the following groups: whether the visits were only pre-delivery or only post-delivery or both, and whether the woman received all five visits, only four, three or two or less visits. However, the main analysis will be based on intention to treat so women who are enrolled in an intervention area, but move to a control area for delivery, will be included in the intervention group.

In addition, analysis will also be done of the mean practice score (a numerical outcome) will be carried out using random effects (multilevel) models that explicitly model the similarity between individuals in the same cluster; (these are not suitable for binary outcomes).

For all statistical determinations, significance levels will be established at 5% level of significance. Coefficient of variation will be reported.

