## Discussions

This study is an effectiveness study designed to directly influence policy. Therefore implementation will be done in close consultation with policy makers and there will be ongoing feedback with preliminary findings. In addition, we will also share the study materials with all interested parties even well before the final evaluation is made. There will be close documentation of all implementation steps, challenges, innovations and experiences occurring at both the demand and supply sides. In addition, the study will be costed as this is important for influencing the policy agenda.

The study has some limitations mainly related to lack of power to measure mortality impact. Another limitation is that the study is implemented in a small area where the risk of contamination is high.

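### Word-of-mouth spillover into control villages is not a secular trend: it shrinks the arm difference and would be credited to facility strengthening in the control before-after analysis

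*Protocol article*

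**What the plan says.** Randomization (under Overview of the trial design) gives the expectation that "we never anticipated contamination to be a big problem, since that would imply making extra home visits". It adds: "This, however, would be monitored in the annual coverage surveys proposed". It then deals with talk between women: "Spillover by word of mouth woman-to-woman or other would be captured as a secular trend in the comparison villages".

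Two later sections read differently. Discussions lists as a limitation that "the study is implemented in a small area where the risk of contamination is high". Additional analyses states that "it is envisaged that there may be significant movements across the arms of the trial", because women go to parents or in-laws for delivery. It adds "This movement can be tracked using our surveillance system" and keeps women in the arm where they were enrolled.

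Hypothesis testing makes intention-to-treat by village of residence the primary analysis, with the effect reported as a relative risk. Data analysis and Additional analyses also plan a before-after comparison within the control area, meant to isolate the effect of improving health facilities alone. Data collection for quantitative surveys provides twice-yearly practice surveys that ask about contact with CHWs.

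**The concern.** The Randomization sentence presents a source of bias as something the design already absorbs. A secular trend is background change shared by both arms. Spillover is part of what the intervention does, delivered to the wrong villages. Several primary outcomes are knowledge or simple home practices (danger signs, cord care, delayed bathing, skin-to-skin contact), which can pass from one woman to another without any CHW visit.

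Two conclusions are at stake. The first is the arm difference, if it is taken as the effect of home visits against no home visits. The second is the control-arm change over time, if it is taken as the effect of facility strengthening. Both feed the scale-up advice that the trial exists to give.

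**Working it through.** **1. Where each component goes.** On the difference scale, let p0 be the control proportion without spillover, E the CHW effect, T the background trend, F the effect of facility strengthening (given to both arms) and f the share of E that reaches controls.

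- Intervention villages change by T + F + E.
- Control villages change by T + F + fE.
- Arm difference = (T + F + E) − (T + F + fE) = (1 − f)E. T cancels; fE does not.
- Control before-after change = T + F + fE. The plan reads this as F. It also contains T and fE, and nothing in the article separates the three.

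Calling fE a secular trend treats it as part of T. T cancels in the arm difference and fE does not, so the label is wrong.

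**2. The sections side by side.** Randomization equates contamination with extra home visits and expects little of it. The same paragraph then names word of mouth, which needs no extra visit. Discussions calls the risk high because the area is small, and Additional analyses expects sizeable movement between arms. Word of mouth, movement and the small area are the routes that the text supports.

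**3. The plan's own sample size.** Sample and sample size gives 60, 25 and 30 interviews per cluster for ANC at least four times (40% to 60%), skilled attendance (30% to 50%) and postnatal care (12% to 24%), with k = 0.25 and 80% power. The two-sided 5% level is my reading. The Hayes-Bennett formula is

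c = 1 + (1.96 + 0.84)² × [p0(1−p0)/m + p1(1−p1)/m + k²(p0² + p1²)] / (p1 − p0)².

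With c = 9 per arm (18 parishes halved, which is an inference), solving for m gives 58.0, 23.6 and 28.3. The stated figures are reproduced to within 2 interviews, and they contain no allowance for dilution.

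**4. Size under assumed f.** The article gives no value for f. For ANC at least four times, E = 20 points:

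| f | Control proportion | Arm difference | Relative risk | Spillover inside control before-after change | Power, 9 parishes per arm, m = 60 | Power, same interviews over 31 villages per arm |
|---|---|---|---|---|---|---|
| 0 | 40% | 20 points | 1.50 | 0 points | 80% | 99% |
| 10% | 42% | 18 | 1.43 | 2 | 70% | 98% |
| 20% | 44% | 16 | 1.36 | 4 | 59% | 94% |
| 30% | 46% | 14 | 1.30 | 6 | 47% | 86% |

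Worked row, f = 20%: control = 40 + 0.20 × 20 = 44%; difference = 60 − 44 = 16 points; relative risk = 60/44 = 1.36; spillover in controls = 0.20 × 20 = 4 points. The last column spreads 9 × 60 = 540 interviews per arm over 31 villages (about 17 each), keeping k = 0.25.

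**5. Movement in both directions.** If a share g of women in each arm takes on the other arm's level, the difference is 20 × (1 − 2g): 16 points at g = 10% and 12 points at g = 20%. These shares are also assumptions.

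**The case against.** The best defence is that the article does not hide contamination. Randomization promises monitoring, the practice surveys ask about CHW contact, movement is tracked, analyses by number of visits are planned, and Discussions admits the limitation. Randomization can also be read as making two separate statements, one on extra visits and one on talk, with the label meaning only that a rise in controls would be seen. All of this stands, so it would be wrong to infer that contamination is simply dismissed. But seeing a rise in controls does not identify its cause. The survey item as described covers home visits, not messages heard from neighbours, and grouping women by visits received is not randomised.

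Other stronger inferences are tempting and not supported:

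- *That intention-to-treat is invalid.* It remains a valid analysis of the effect as assigned. Only the effect against no exposure is understated, and only if spillover improves control practices, which is the natural direction here.
- *That a null result would be misread under a stated rule.* The article states no rule for reading a null. On the village basis, power for ANC is still 94% at 20% spillover, so modest spillover need not produce one.
- *That lead CHWs or facility staff carry the intervention to controls.* Lead CHWs "coordinate the work of fellow CHWs in their respective parishes and communicate to the health workers any developments in the community"; contact with control women is an inference. Health-worker training is given to both arms by design.
- *That annual and twice-yearly surveys contradict each other.* One is called a coverage survey and the other a practice survey; they may be different instruments.

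**Conclusion.** The point holds in a limited form. The secular-trend sentence is wrong in principle. Its most concrete consequence is in the control before-after analysis, where spillover and background trend would both be credited to facility strengthening. The arm difference is likely to be conservative for the effect against no CHW exposure. The expectation in Randomization also conflicts with Discussions and Additional analyses.

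The size cannot be derived from the article. If 10% to 30% of the effect reaches controls, a true 20-point difference appears as 18 to 14 points, and 2 to 6 points of control-arm change are misattributed. The loss of power depends on the cluster basis: marked with 9 parishes per arm, milder with 31 villages. The direction of the distortion is therefore firmer than any prediction of a missed effect. This should be corrected, but it does not undermine the primary analysis.

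**What to change.** - Delete the secular-trend sentence and reconcile the contamination statements in Randomization with Discussions and Additional analyses.
- State that intention-to-treat remains the primary analysis of the effect as assigned and is likely conservative for the effect against no exposure.
- State that the control before-after change mixes facility strengthening, background trend and spillover, and cannot be read as facility strengthening alone.
- Tabulate CHW exposure among control women from each practice survey, noting that home-visit exposure misses word of mouth.
- As an exploratory analysis with the existing GIS data, show control-village outcomes by distance to the nearest intervention village. With 32 control villages the intervals will be wide, and distance may be confounded by remoteness and village density; say so.

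The article says the detailed analysis plan is still to be finalised, so the last two items can go there. The cost is some wording, a little analysis on data already collected, and a more cautious interpretation of a small arm difference and of control-arm change.
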